## Abstract

**Introduction:**

Obesity is a global health crisis associated with significant physical and cognitive impairments, particularly in executive function. Impaired executive function exacerbates unhealthy eating behaviors and hinders effective weight management. Non-invasive neuromodulation techniques like transcranial direct current stimulation and transcranial magnetic stimulation have demonstrated potential in improving executive function and assisting in weight reduction but face limitations in accessibility and efficacy. Low-intensity pulsed ultrasound (LIPUS) represents an emerging neuromodulation technique distinguished by its non-invasive application and superior spatial resolution, facilitating targeted modulation of cortical activity and neural excitability with high precision. This study aims to explore the efficacy of LIPUS on executive function in obesity.

**Methods and analysis:**

This study adopts a prospective, single-center, double-blind, randomized controlled design. A total of 44 participants diagnosed with obesity (BMI ≥ 28 kg/m^2^) will be enrolled and equally assigned to the LIPUS and sham groups. The LIPUS group will receive pulsed therapeutic ultrasound for 4 weeks, while the sham group will receive placebo treatment using a device delivering no therapeutic ultrasound. Both groups will undergo assessments at baseline and after 4 weeks, with the primary outcome being the change in reaction time on the food Go/No-go task. Secondary outcomes include changes in body weight, BMI, food cravings (measured by the Food Craving Questionnaire-Trait and State versions), food-eating behavior (measured by the Visual Analog Scale and the Dutch Eating Behavior Questionnaire), and cognitive performance as assessed by the Stroop test. Additional neuroimaging assessments will include functional near-infrared spectroscopy (fNIRS), functional magnetic resonance imaging (fMRI), and electroencephalography (EEG).

**Discussion:**

This trial will be the first to evaluate LIPUS for enhancing executive function in individuals with obesity. By combining wearable ultrasound technology with neuroimaging assessments, the study is expected to provide novel evidence for the neuromodulatory role of LIPUS. The results may support the development of innovative, non-invasive strategies for obesity management and inform future clinical applications.

## 1 Introduction

Obesity, characterized by an excessive accumulation of fat tissue that negatively impacts health, has been escalating into a global health crisis, posing significant challenges to public health systems (Lin and Li, 2021). According to the World Health Organization, obesity rates more than doubled between 1990 and 2022 (Obesity and Collaborators, 2024), reflecting its widespread impact across various age groups and socioeconomic backgrounds. Beyond its well-documented physical consequences, such as cardiovascular diseases and type 2 diabetes (Piché et al., 2020; Caballero, 2019; Seravalle and Grassi, 2017), obesity is increasingly recognized for its adverse effects on cognitive functions, with growing evidence linking excess body fat to impairments in memory, attention, and executive function (Mattson, 2019; Lowe et al., 2019). Conversely, the decline in executive function, which governs planning, decision-making, and self-regulation, can make it more difficult for individuals to adhere to healthy behaviors, such as managing diet and exercise, contributing to a vicious cycle of weight gain and reduced quality of life (Doebel, 2020; Yang et al., 2018). Thus, the decline of executive function in obesity, as a crucial cognitive domain, calls for immediate focus and intervention from both public health organizations and healthcare professionals.

Executive function plays a crucial role in translating healthy eating principles into daily behaviors and sustaining the behavioral changes necessary to overcome obesity (Yang et al., 2018). Evidence suggests that deficiencies in executive function, especially with cognitive flexibility and inhibitory control, are closely associated with poor weight management outcomes (Foldi et al., 2021). Despite the growing recognition of its importance, effective interventions specifically targeting executive function deficits in individuals with obesity remain limited. Evidence highlights that the dorsolateral prefrontal cortex (DLPFC), a neural hub responsible for executive function regulation and control, typically shows reduced activation after meals in obese individuals compared to lean individuals (Le et al., 2007). Moreover, evidence indicates that enhancing DLPFC activity can improve decision-making, impulse control, and dietary compliance among individuals with obesity (Gluck et al., 2017; Kringelbach et al., 2004). Therefore, developing interventions to modulate DLPFC activity holds promise for addressing executive function-related impairments in obese population, which may help accelerate the prevention and treatment of obesity.

In recent years, non-invasive brain stimulation techniques, such as transcranial direct current stimulation (tDCS) and transcranial magnetic stimulation (TMS), have shown potential in improving cognitive function and eating behavior in obesity (Kekic et al., 2014). For instance, home-based tDCS targeting the dorsolateral prefrontal cortex (DLPFC) was shown to significantly reduce uncontrolled and emotional eating in patients with fibromyalgia (Jornada et al., 2024), while Anderson et al. (2023) reported that tDCS over the DLPFC altered the perceived pleasantness of food stimuli (Anderson et al., 2023). A recent randomized controlled trial further explores tDCS modulation of brain reactivity to food cues in obesity (Ghobadi-Azbari et al., 2022). Similarly, repetitive TMS (rTMS) applied to the left DLPFC improved food craving control and eating behaviors in obese participants and contributed to modest weight reduction (Kim et al., 2018). Despite these encouraging findings, both modalities have notable limitations. The efficacy of tDCS remains inconsistent, largely due to inter-individual variability in neural responsiveness, which hampers its predictability and generalizability (Vergallito et al., 2022; Evans et al., 2020). Similarly, TMS is constrained by limited portability and intrinsic challenges in achieving fine spatial precision and depth selectivity, which may reduce accessibility and hinder accurate targeting of specific cortical regions (Bhattacharya et al., 2022).

Low-intensity pulsed ultrasound (LIPUS) is an emerging non-invasive therapeutic modality that applies ultrasound waves with low intensity and pulsed frequency to stimulate tissues at a cellular level. Traditionally used in musculoskeletal rehabilitation for its ability to promote tissue healing and reduce inflammation (Qin et al., 2023), LIPUS has recently attracted attention for its potential in modulating brain activity and improving cognitive function (Zeng et al., 2022). By fine-tuning parameters such as intensity, frequency, pulse width, and duration, LIPUS enables bidirectional modulation of targeted brain areas (Dallapiazza et al., 2018), including the DLPFC. Compared to traditional neuromodulation techniques, LIPUS offers deeper tissue penetration and localized stimulation without the need for invasive procedures (Tufail et al., 2011). Moreover, LIPUS operates intermittently, minimizing thermal effects and allowing precise stimulation without damaging surrounding healthy tissue (Fomenko et al., 2018). Research has demonstrated the potential of LIPUS to improve cognitive function in diverse groups, including individuals with Alzheimer’s disease (Shimokawa et al., 2022), as well as those with traumatic brain injury (Wang W. et al., 2024; Su et al., 2017). However, no studies have yet investigated the application of transcranial ultrasound therapy for improving executive function in individuals with obesity.

Therefore, the purpose of this study is to explore the efficacy of LIPUS as a potential non-invasive intervention to improve executive function in obesity, utilizing a self-developed wearable LIPUS device specifically designed for this purpose. We hypothesize that 4 weeks of daily LIPUS stimulation targeting the DLPFC will enhance executive function, as reflected by shorter reaction time in the Food Go/No-go task in the LIPUS group, whereas no significant changes are expected in the sham group. Furthermore, these improvements in executive function are expected to facilitate reductions in body weight and BMI.

## 2 Methods

### 2.1 Study design

This trial is a prospective, single-center, double-blind randomized controlled trial (RCT) to be conducted at the Shanghai Jiao Tong University of Medicine Affiliated Sixth People’s Hospital. Eligible participants will be identified based on a diagnosis of obesity (BMI ≥ 28 kg/m^2^) according to Chinese criteria (Zeng et al., 2021). Participants will be evenly randomized in a 1:1 ratio into either the LIPUS group or the sham group. The trial design will be conducted following the Standard Protocol Items: Recommendations for Interventional Trials guidelines (SPIRIT; Chan et al., 2013), and the detailed study workflow is depicted in Figure 1.

**FIGURE 1 F1:**
[figure not shown]
Participant flow chart.

### 2.2 Participant and public involvement

Participants and the general public were not directly involved in framing the research question, selecting outcome measures, designing the study, recruiting participants, or overseeing its implementation. However, upon the completion of the trial, results will be shared with participants and the public through accessible formats.

### 2.3 Participant recruitment

A total of 44 participants diagnosed with obesity (BMI ≥ 28 kg/m^2^) will be enrolled and equally assigned to the LIPUS and sham groups. Recruitment is scheduled to commence on 10 December 2024 and continue over a span of 15 months or until the target sample size is achieved. Recruitment activities will be conducted through the endocrinology outpatient clinics at Shanghai Jiao Tong University of Medicine Affiliated Sixth People’s Hospital, Shanghai, China. Prospective participants and their guardians will be invited to an in-person meeting, during which the study’s objectives, procedures, potential benefits, and any associated risks or discomforts will be explained in detail. Participants will be required to provide written consent before being formally enrolled in the study.

### 2.4 Inclusion/exclusion criteria

#### 2.4.1 Inclusion criteria

BMI ≥ 28 kg/m^2^ and <35 kg/m^2^;Aged 18–60 years, inclusive;The subject or the subject’s family agrees and signs an informed consent form, being able to cooperate with various examinations during the clinical research period.

#### 2.4.2 Exclusion criteria

History of head trauma or epilepsy, or a family history of epileptic seizures;Presence of implanted metal devices, pacemakers, claustrophobia, or any other contraindications to functional magnetic resonance imaging (fMRI);Existence of diabetes mellitus or unstable cardiovascular diseases;Greater than 5% change in body weight within the past 3 months;Receipt of weight loss treatment within the past 6 months;Diagnosis of psychiatric disorders or current use of psychotropic medications;Abnormal findings on brain magnetic resonance imaging (MRI);Severe hepatic or renal dysfunction;Inability to communicate with researchers or staff, or participation in other clinical studies simultaneously.

### 2.5 Medical evaluation and enrollment procedure

Participants will undergo a screening process to assess their eligibility for the trial. This will include a thorough health history review and a physical examination to ensure they meet the inclusion criteria and do not have any conditions that would exclude them from participation.

Following the medical evaluation, baseline data will be collected from all eligible participants, including demographic information (age, gender, and occupation), lifestyle habits (smoking and alcohol consumption), body weight, body mass index (BMI), and medical history. Also, participants will be assessed using the food Go/No-go task and the Stroop task, as well as rating scales including the Food Cravings Questionnaire-Trait (FCQ-T) and Food Cravings Questionnaire-State (FCQ-S), visual analog scale (VAS), Dutch Eating Behavior Questionnaire (DEBQ). Other medical examinations will be performed, including functional near-infrared spectroscopy (fNIRS), electroencephalogram (EEG), and functional magnetic resonance imaging (fMRI).

### 2.6 Randomization and blinding

Randomization will be carried out by an independent statistician, who is not involved in the implementation or analysis of this trial, using a random number table generated by the Microsoft Excel. Participants will be randomly assigned to either the LIPUS group or the sham group in equal proportions (1:1) using a block randomization method. To ensure allocation concealment, group assignments will be sealed in opaque, sequentially numbered envelopes.

Blinding will be maintained for both participants and study staff involved in data collection, outcome assessment and statistical analysis. All LIPUS treatment devices are equipped with a vibration mode, rendering no discernible difference between the LIPUS and sham group during the trial. Blinding integrity will be verified periodically during the trial to ensure adherence.

### 2.7 Intervention

Participants will perform LIPUS therapy independently at home over a 4-week period, utilizing a self-developed wearable device (Figure 2). The LIPUS group will receive pulsed therapeutic ultrasound, targeting the bilateral DLPFC projections on the scalp. The LIPUS device operates at a frequency of 600 kHz with an effective intensity of 1.0 W/cm^2^ and a 50% duty cycle (10 ms on, 10 ms off). Two transducers work alternately (each active for 1 s) during a 20-min treatment session, maintaining the treatment-site temperature below 41 °C to ensure safe and stable acoustic stimulation (Hayner and Hynynen, 2001; Zhang et al., 2021; U.S. Food and Drug Administration, 2019; Fomenko et al., 2020; Legon et al., 2020; Pellow et al., 2024). Each session will last 20 min, performed daily over 4 weeks. Treatment settings will remain unchanged throughout the trial unless the participant’s condition worsens or adverse effects are observed. The sham group will use a device identical in appearance and operation to the LIPUS group’s device but delivering no therapeutic ultrasound. All participants, regardless of group allocation, will receive standardized guidance on a low-calorie diet and maintenance of their habitual physical activity. This guidance is consistent with participants’ usual routines, and no additional dietary or exercise interventions will be applied. Participants will remain at home throughout the study, and will be asked to maintain daily logs of food intake and physical activity, which will be collected and reviewed regularly by the study team throughout the study period, ensuring that any observed differences in outcomes can be attributed to LIPUS stimulation.

### 2.8 Data management

As outlined in Table 1, data will be systematically collected at baseline, and at the second and fourth weeks of the treatment period. All paper-based materials, including the study protocol, case report forms and informed consent forms will be securely stored by the principal investigator in a locked box at Shanghai Jiao Tong University of Medicine Affiliated Sixth People’s Hospital. All electronic data will be securely recorded in a password-protected electronic database, accessible only to authorized team members. Participant withdrawal from the study will be permitted under specific conditions, such as voluntary withdrawal of consent or the identification of exclusion criteria post-enrollment. For all withdrawals, the reasons and dates will be meticulously documented.

**TABLE 1 T1:** Study evaluation procedures and timeline.

Study procedure	Medical evaluation	Enrollment visit	2 weeks	4 weeks
Determine eligibility	√	√		
Obtain signed consent		√		
Other medical and demographic data		√		
Give instructions for LIPUS devices		√		
**Outcome measures**				
Food Go/No-go task		√	√	√
Body weight, BMI		√	√	√
FCQ/T, FCQ/S, VAS, DEBQ scale		√	√	√
Stroop task		√	√	√
EEG		√	√	√
fNIRS		√	√	√
fMRI		√		√

### 2.9 Outcome measures

An outline of the study outcome assessments and corresponding descriptions of their purposes is presented in Table 2.

**TABLE 2 T2:** Outcome assessments and their respective purposes.

Outcome measures	Assessment type	Purpose description
Food Go/No-go task	Primary outcome	To assess food-related inhibitory control
Body weight and BMI	Secondary outcome	To monitor physical changes related to the intervention
FCQ-T and FCQ-S	Secondary outcome	To evaluate long-term and situational food cravings, respectively
VAS	Secondary outcome	To measure appetite and hunger perceptions
DEBQ	Secondary outcome	To assess habitual patterns of emotional, external, and restrained eating
Stroop task	Secondary outcome	To measure cognitive flexibility and selective attention
fNIRS	Secondary outcome	To measure task-related hemodynamic responses in the cortical surface
EEG	Secondary outcome	To monitor cortical activity during ultrasound neuromodulation of the DLPFC
fMRI	Secondary outcome	To evaluate changes in brain structure and connectivity

LIPUS, low-intensity pulsed ultrasound; BMI, body mass index; FCQ-T, Food Cravings Questionnaire-Trait; FCQ-S, Food Cravings Questionnaire-State; VAS, visual analog scale; DEBQ, Dutch Eating Behavior Questionnaire; EEG, electroencephalography; fNIRS, functional near-infrared spectroscopy; fMRI, functional magnetic resonance imaging.

#### 2.9.1 Primary outcome measures

The primary outcome is the difference in mean reaction time change on the food Go/No-go task from baseline to the fourth week of treatment (LIPUS group vs. sham group). The Go/No-go task is a well-recognized experimental paradigm for assessing executive functions (Raud et al., 2020; Foland-Ross et al., 2019). The food Go/No-go task is a modified version designed specifically to assess food-related inhibitory control (He et al., 2019; Wang K. et al., 2024). Key indicators for assessment include reaction time and the number of erroneous responses (Labonté and Nielsen, 2023). Shorter reaction time and fewer erroneous responses are indicative of better executive function.

In this study, each participant will complete six blocks, which are randomly assigned in equal numbers to three experimental conditions: (1) low-calorie food Go, (2) high-calorie food Go, and (3) neutral item Go. In the low-calorie food Go condition, participants are instructed to press a key in response to low-calorie food images while inhibiting responses to high-calorie food images. Conversely, in the high-calorie food Go condition, participants respond to high-calorie food images and inhibit responses to low-calorie food images. In the neutral item Go condition, participants respond to neutral non-food images and inhibit responses to all food-related images.

Each block consists of two phases: a Go-only phase (8 trials) followed by a Go/No-go phase (32 trials, Go: No-go ratio = 3:1). Each stimulus is presented for 500 ms, followed by a 1000 ms fixation cross. The interval between the Go-only and Go/No-go phases is 3 s, and the inter-block interval is 20 s. As a result, each block lasts 63 s, and the total task duration is 498 s.

During the task, mean reaction time for correct Go trials and commission error rates for No-go trials are recorded. In addition, fNIRS is employed to capture cortical hemodynamic responses, enabling further investigation of neural activity patterns under different task conditions. The flow of the paradigm is shown in Figure 3.

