### 2.11 Sample size calculation

The sample size calculation was based on the primary outcomes. *A priori* power analysis was conducted using G*Power. Drawing from the previous trial, an F effect size of 0.25 was selected, with a conservative correlation of 0.4 between repeated measures and non-sphericity correction of 1 (Stinson et al., 2022; Kang, 2021; Wen et al., 2024). The statistical power was targeted at 80%, with a two-sided significance level (α) of 0.05. Using PASS software, the required sample size per group was determined to be n1 = n2 = 20. Considering a potential dropout rate of 10%, the adjusted total sample size includes 44 participants, evenly distributed between the two groups.

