### 2.12 Analysis plan

#### 2.12.1 Statistical analysis

Data will be processed and analyzed using SPSS 26.0. Continuous data will be summarized as means and standard deviations if they follow a normal distribution; otherwise, medians and interquartile ranges will be reported. Categorical variables will be presented as frequencies and percentages. To compare continuous data between groups, independent samples *t*-tests will be used for normally distributed variables, while non-parametric tests will be applied for data that do not meet normality assumptions. For categorical data, group differences in proportions will be assessed using chi-square tests or Fisher’s exact test, depending on the data characteristics. A repeated-measures ANOVA will be conducted to evaluate outcome variables between the two groups across the three assessment time points. For the primary outcome, measured by the food Go/No-Go task, will be analyzed using an intention-to-treat approach, which includes all randomized participants. Sensitivity analyses will be conducted using per-protocol sets to examine data from participants who completed the trial as planned and adhered to the protocol, as well as full analysis sets to evaluate the robustness and generalizability of the results. Additionally, safety sets will be utilized to analyze adverse events throughout the trial.

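### The primary comparison of reaction-time change makes no use of baseline as a covariate; at the plan's own correlation of 0.4, adjusting for it would cut the variance by about 28% at no cost in data

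*Protocol article*

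**What the plan says.** Section 2.9.1 of the protocol article defines the primary outcome as the "difference in mean reaction time change on the food Go/No-go task from baseline to the fourth week of treatment (LIPUS group vs. sham group". This is a contrast of change scores.

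Section 2.11 sizes the trial on these inputs: "an F effect size of 0.25 was selected"; "conservative correlation of 0.4 between repeated measures and non-sphericity correction of 1"; "The statistical power was targeted at 80" percent; "two-sided significance level (α) of 0.05". The result is that "the required sample size per group was determined to be n1 = n2 = 20", raised to 44 in total for 10% dropout. The number of time points behind the calculation is not given.

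Section 2.12.1 names the analyses. One sentence begins "To compare continuous data between groups, independent samples" and goes on to t-tests, or non-parametric tests where normality fails. Another names a repeated-measures ANOVA of the two groups over the three assessments. Neither mentions ANCOVA or a baseline covariate. Baseline reaction time is collected from every participant at enrollment (section 2.5 and Table 1).

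**The concern.** Subtracting the baseline is not the same as adjusting for it. Subtraction forces a slope of 1 on the baseline value, whereas the slope implied by the plan's assumptions (equal variances, correlation 0.4) is 0.4. With a correlation that low, subtraction adds more noise than it removes, and the change score is less precise than the week-4 value on its own. A repeated-measures ANOVA does not help, because it treats baseline as one more outcome rather than as a covariate.

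Precision on the primary outcome is at stake in a trial of 44 people, whose small size the discussion lists as a limitation. The information needed to recover that precision is already being collected.

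**Working it through.** **Inputs.** All are from section 2.11: f = 0.25, correlation ρ = 0.4, non-sphericity correction 1, two-sided α = 0.05, target power 80%, 20 per group (N = 40). Variances at baseline and week 4 are taken as equal (σ² = 1), and 0.4 is taken as the baseline/week-4 correlation. Both follow the structure of the plan's own calculation.

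**Step 1: reproduce the plan's figure.** For the group-by-time interaction with m time points, the noncentrality is λ = f²·N·m/(1−ρ), with (m−1) and (N−2)(m−1) degrees of freedom.
- m = 2: λ = 0.0625 × 40 × 2 / 0.6 = 8.33 on 1 and 38 df, power 80.3%. The smallest adequate N is 40, an exact match.
- m = 3: the smallest N is 34.
- Between-groups main effect: N = 90 (m = 2) or 78 (m = 3).

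Only the two-time-point interaction gives 40, and with two time points that interaction is the t-test on change scores. In that layout f equals the between-group difference in change divided by 4 (in SD units), so f = 0.25 corresponds to 1.0 SD.

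**Step 2: variances per participant.**
- Change score: 2(1−ρ) = 2 × 0.6 = 1.20
- Week-4 value alone: 1.00
- Baseline-adjusted (ANCOVA): 1−ρ² = 1 − 0.16 = 0.84

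The ratio of ANCOVA to change is 0.84/1.20 = (1+ρ)/2 = 0.70, a 30% reduction. Estimating the slope multiplies the ANCOVA variance by about 1 + 1/(2n−4) = 1 + 1/36 = 1.028 at n = 20 per group. The ratio becomes 0.70 × 1.028 = 0.72, and simulation gives 0.716. The realistic reduction is therefore about 28%.

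**Step 3: power at 1.0 SD, 20 per group, ρ = 0.4** (noncentral F, one error df lost for ANCOVA).

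| Analysis | Power | n per group for 80% | Difference detectable with 80% power |
|---|---|---|---|
| Change score | 80.3% | 20 | 0.996 SD |
| Week 4 alone | 86.9% | 17 | 0.909 SD |
| ANCOVA | 91.9% | 15 | 0.834 SD |

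Simulation with the slope estimated gives 91.0% for ANCOVA.

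**Step 4: dependence on the correlation** (ANCOVA against change, 20 per group, effect 1.0 SD).

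| ρ | Ratio in theory | Ratio with slope estimated | Power, change | Power, ANCOVA |
|---|---|---|---|---|
| 0.4 | 0.70 | 0.72 | 80% | 92% |
| 0.6 | 0.80 | 0.82 | 93% | 97% |
| 0.8 | 0.90 | 0.92–0.93 | above 99% | above 99% |
| 0.95 | 0.975 | 1.00 | – | – |

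**Step 5: the three-time-point ANOVA named in section 2.12.1.** Its interaction has 2 df and is a different test from the t-test on change. Let the group differences at baseline, week 2 and week 4 be 0, w and 1.0 SD, and let S be the sum of their squared deviations from their own mean. Then f² = S/12.
- w = 0.5: S = 0.5, f² = 0.0417, λ = 0.0417 × 120 / 0.6 = 8.33 on 2 and 76 df, power about 72%.
- w = 1.0: S = 0.667, f² = 0.0556, λ = 11.1, power about 84%.

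For the same week-4 effect, its power therefore depends on an unstated week-2 effect, and it too leaves baseline unadjusted.

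**The case against.** **Nothing here is invalid.** A reader might infer that chance baseline imbalance biases the change-score comparison through regression to the mean. The documents do not support that: allocation is randomized 1:1, so the comparison is unbiased. With 22 per arm, a one-standard-error imbalance is √(2/22) = 0.30 SD and would shift the estimate by 0.6 × 0.30 = 0.18 SD, but such shifts average to zero and are already counted in the variance of 1.20. Nor is the trial underpowered on this account, since 20 per group gives the change-score test its stated power. This objection stands in full.

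**The correlation is a cautious planning value.** Section 2.11 itself calls 0.4 conservative. If the true value exceeds 0.5, the change score is more precise than week 4 alone, and the advantage of ANCOVA shrinks as Step 4 shows. It would be too strong to say that ANCOVA wins at every correlation below 1: at 20 per group the advantage is gone by about 0.95. This stands, and is why the gain is given as a range.

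**Endpoint and estimator differ, and the article is condensed.** A change endpoint is compatible with baseline adjustment, the t-test sentence is generic, and an analysis plan that is not shown could name the covariate. This stands in part. The article does not merely stay silent: it names the tests, none of them adjusts for baseline, and its sample size matches the unadjusted change-score test.

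**Conclusion.** The planned comparison is sound but leaves precision unused. At the plan's own correlation of 0.4, baseline adjustment lowers the variance of the primary contrast by 30% in theory and about 28% in practice. Power at a 1.0 SD effect rises from about 80% to about 92%, or equivalently the detectable difference falls from 0.996 to 0.834 SD. The gain is about 18% in variance at a correlation of 0.6 (power 93% to 97%), about 8% at 0.8, and nil at about 0.95.

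This rests on equal variances, on 0.4 standing for the baseline/week-4 correlation, and on the inference that section 2.11 used two time points. The figures for the change-score test do not carry over to the three-time-point ANOVA. The point is a free improvement: it shows neither bias nor a shortfall in the planned sample size.

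**What to change.** In section 2.12.1, state before unblinding that the primary week-4 contrast is tested by ANCOVA, or by a mixed model, with baseline reaction time as covariate and treatment group as factor. The change endpoint of section 2.9.1 need not be altered: with baseline in the model, the treatment estimate is identical whether the response is the change or the week-4 value. The same sentence would settle which of the listed tests carries the primary contrast.

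Use the same adjustment for Stroop, FCQ, VAS and DEBQ. For body weight and BMI, little gain is to be expected if their baseline/week-4 correlation is near 1, which is an assumption the documents neither give nor exclude.

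The cost is one sentence and one error degree of freedom, with no new data, visits or participants.
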